### Feasibility

The feasibility of the study design was examined as part of a master’s thesis by one of the study assistants. For this purpose, the first study round was evaluated for the effectiveness and feasibility of the interventions, as well as the satisfaction with the therapy from the perspective of the participants and therapists. The results of the work showed high feasibility of the study design, high satisfaction with the therapy, and trends indicating effectiveness of the treatment for anxiety disorders. The detailed results of the feasibility study can be found in the master’s thesis of [52].

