
### Randomization and blinding

With the help of the online platform randomizer.org participants will be randomly allocated to three test conditions right after they completed the PRE-evaluation form. The allocation is random and independent of the diagnosis or other criteria. The externally recruited therapists will be blindly assigned to the treatment conditions. Neither the participants nor the practitioners were allowed to decide which group they were assigned to. The authors, who also act as therapists, will conduct the control group to prevent falsification effects in the intervention groups. Statistical analyses will be conducted by the principal investigator, who will not be blinded or independent.

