### Interventions

The first step in conducting the study was the development of the treatment manuals and therapy materials. Two treatment manuals were developed, one each for PPT and CBT treatment. The PPT manual is based on the official PPT manual by [10] and adapted for the study. Because of economic reasons instead of 15 sessions as in the original manual, only 10 therapy sessions are conducted in the present study. In addition, the individual PPT topics were adapted and exercises from the personal PPT application repertoire of the study leaders were incorporated. As in the original manual, a gratitude diary will be filled out daily by the participants accompanying the therapy. In the individual sessions, various positive-psychological interventions are carried out, e.g., participants learn how to handle and use positive emotions, work out their personal character strengths and learn how to use them in concrete anxiety situations. Other topics covered in the PPT treatment include gratitude, optimism, a positive self-image, self-compassion, resilience, everest goals, best-possible self, and future perspective. The CBT manual is conceptually adapted to the PPT treatment and also comprises 10 therapy sessions. The exercises and content were selected based on the German language therapy tools for anxiety disorders by [56]. In the CBT treatment, participants are required to practice the relaxation exercise Progressive Muscle Relaxation according to Jacobsen on a daily basis. In CBT treatment, participants learn how to deal with anxiety thoughts and behavior and how to restructure stressful anxiety related cognitions. For this purpose, various cognitive-behavioral therapy interventions are carried out, e.g., the development of an individual explanatory model, the worry chair and various attention and breathing exercises. An elementary part of the treatment is an exposure exercise, which is worked towards during therapy. Other topics covered in CBT treatment include the three levels of anxiety (body, thoughts, behavior), the vicious cycle of anxiety, and mindfulness. In addition to the treatment manuals, workbooks were created for the participants to work on during the therapy. The workbooks contain all organizational details, theoretical topics as well as all exercises and worksheets that must be done in the video-supported sessions or as homework. Additional websites (created by Webflow) were provided for both intervention groups to make additional therapy tools available, such as videos or questionnaires. That aside the websites are also used to conduct part of the data collection. The implementation of the treatments takes place online via videoconferencing using the Zoom platform. Participants in the two intervention conditions (PPT & CBT) will meet once a week with the treatment providers for a 120-minute online presence meeting, in which the content of the respective sessions will be conducted according to the manual. In addition, participants will be given homework assignments to complete independently for the week between the face-to-face sessions. These homework assignments will be discussed in the group at the beginning of each session. The control group is designed as a PPT with minimal therapeutic supervision. The participants will receive the same PPT workbook as the intervention group and accordingly will work on the same topics and exercises over the ten weeks as the participants in the PPT intervention group. The difference between the two groups lies in the therapeutic support. In the control group, a video-supported meeting with the therapist will be held only three times: In the first session, halfway through therapy in the fifth session, and in the last session. In between, participants receive an overview email at the beginning of the week and a reminder email at the end of the week. Apart from the possibility of mail contact with the therapists, the participants in the control group carry out the exercises independently with the help of the workbook and the materials on the website. For the control group, as for the intervention groups, a separate website is provided. Another important component of all treatment conditions is the formation of teams of two clients (couple teams) within each therapy group. These teams will be formed in the first session of therapy and will remain in place throughout the duration of therapy. Participants are encouraged to meet at least once a week to discuss the week’s exercises and topics with each other. In some cases, specific reflection questions will be provided in the individual exercises in the workbook. Depending on the possibilities of the participants, the meeting could take place online via a telephone call or video call or in person. When forming the couple teams, deliberate care was taken to divide the participants according to local proximity.

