### Trial governance

The Trial Management Group consists of the principal investigator, the study director ([name]) and is supported by two study assistants. The Management Group will provide overall management of the study including set-up of the study, recruitment, managing mails, and interpretation of results. In addition, eleven therapists (psychological psychotherapists in training) support the study by conducting the therapy groups. In preparation for the study, therapy manuals, websites and workbooks were developed for the different intervention groups by the principal investigator, the study director and a study assistant. Overall supervision of the trial is provided by the principal investigator. The therapists were trained in the manuals and for screenings by the project management. All therapists were trained in both manuals in order to be able to adopt both intervention groups (PPT and CBT) as needed during the course of the various study runs. At regular intervals, the therapy sessions are checked for their manual compliance and the therapists receive supervision by qualified psychotherapists and supervisors.

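### The principal investigator, who co-developed the treatments, will analyse the trial unmasked while lead scale, contrast and time point are open; coded arms and a locked script would cheaply limit result-driven choice

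*Protocol article*

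**What the plan says.** Randomization and blinding assigns the analysis outright: "Statistical analyses will be conducted by the principal investigator, who will not be blinded or independent". The same section adds: "The authors, who also act as therapists, will conduct the control group".

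Trial governance states that "therapy manuals, websites and workbooks were developed for the different intervention groups by the principal investigator, the study director and a study assistant". It also places interpretation of results with the Trial Management Group, of which the principal investigator is a member. Interventions says of the PPT manual that "exercises from the personal PPT application repertoire of the study leaders were incorporated"; it says nothing comparable about the CBT manual.

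Feasibility reports that "the first study round was evaluated for the effectiveness and feasibility of the interventions", that this was "examined as part of a master’s thesis by one of the study assistants", and that it showed "trends indicating effectiveness of the treatment for anxiety disorders".

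On what is to be analysed, Primary outcome measures lists seven questionnaires in three domains. Statistical analysis defines the primary outcome as change to post-treatment and to follow-up in anxiety and positive outcomes, to be tested by intention-to-treat repeated measures ANOVA across the three arms. Table 1 registers the three domains and gives masking as none.

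**The concern.** An analyst who can see which arm is which, and who has a stake in the treatments, can let the emerging results guide what is emphasised: which scale leads, which pair of arms is the headline, whether T1 or T2 carries the conclusion, who is excluded. None of this needs bad faith.

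Participants and therapists cannot be masked to the treatment, and every named questionnaire is self-report. The analysis is therefore one of the few stages where masking is still practicable, and the protocol declines it without giving a reason. At stake is the credibility of a positive statement about PPT, the treatment that carries the study leaders' own exercises.

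**Working it through.** No figure in the protocol can be recomputed for this point. The check is whether the separate statements together leave room for result-driven choice, and whether that room can be sized.

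**1. Roles held by the principal investigator.**
- Co-developer of the manuals, websites and workbooks (Trial governance).
- Overall supervisor of the trial and member of the group that interprets results (Trial governance).
- Sole named analyst, unblinded and not independent (Randomization and blinding).

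**2. What was known early.** Feasibility gives a favourable trend from the first round. It names a study assistant as the evaluator and does not break the trend down by arm. The article does not say whether first-round participants count toward the 165.

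**3. What the text leaves open.**
- Scales: anxiety 4 (BAI, PAS, GAD-7, FQ), happiness 2 (PPTI, FS), quality of life 1 (SWLS). 4 + 2 + 1 = 7, none marked as leading.
- Post-baseline times: 2 (T1, T2). 7 × 2 = 14 scale-by-time results.
- Pairs of arms: 3. The main research question sets PPT and CBT against the control; the Abstract also announces a comparison of CBT with PPT. 14 × 3 = 42 possible headline results.

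**4. What limits it.** Registration is dated 3 February 2022 and first enrolment was planned for 1 March 2022. The three domains therefore precede any first-round data and cannot have been picked from results. The model family and the intention-to-treat principle are named. Inside the domains, the choice among four anxiety scales, two happiness scales, two times and three contrasts remains.

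**5. Can the problem be sized?** The number within reach is the chance of at least one p < .05 when no arm differs.
- Seven independent tests: 1 − 0.95^7 = 0.302.
- Fourteen independent tests: 1 − 0.95^14 = 0.512.
- Fourteen tests simulated with an assumed correlation of .6 between times and 0, .3, .5 or .7 between scales: about .47, .43, .37 and .29.
- The same simulation, counting only results that favour one named arm (one tail at .025): about .27, .22, .19 and .15.

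The correlations are assumptions; the protocol gives none. More importantly, an independent, fully masked analyst who ran the same 14 tests would have exactly these rates. They describe multiple testing, not the effect of an unmasked analyst, so they do not measure this problem.

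**The case against.** The arrangement is openly disclosed, and the case against it can easily be overstated. Several stronger readings are tempting but unsupported.

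- *The team already knows how the arms compare.* Feasibility speaks of one trend for the treatment, which may be a pooled pre-post change. It does not say that the principal investigator ran that evaluation or saw results by arm.
- *Writing the manuals shows allegiance to PPT.* The team prepared materials for both PPT and CBT, and the control arm uses the PPT workbook. Only the study leaders' own exercises point to PPT in particular.
- *The principal investigator treats control participants.* The text says that authors do; it does not identify the principal investigator as one of those therapists.
- *Missing-data and covariate rules are absent.* Those belong in an analysis plan, which may exist but is not shown.
- *The multiple-testing rate is the size of the harm.* It is not, as step 5 shows.

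It can also be said that the outcome section includes a third-party anxiety rating. That does not supply masking: Table 2 assigns it to therapists, who know the treatment they deliver.

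All of these limits stand. What they leave intact is the declared arrangement itself. A separate plan could fix the lead scale, contrast and model. Unless it also masked the arms, it would not alter the statement that the analyst is neither blinded nor independent. Disclosure informs the reader but does not protect the result.

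**Conclusion.** The point holds in limited form. The protocol commits to an unmasked, non-independent analyst who helped build the treatments and helps interpret the results, while its text leaves seven primary scales, two times and three possible contrasts without a lead. Result-driven choice is possible; a reader might infer that it has happened, but the documents give no evidence of that.

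The size of any bias cannot be estimated. The conclusion assumes that no dated analysis plan predating the first-round evaluation already fixes the lead scale, contrast and time point. If one does, most of the freedom is gone and what remains is the missing masking at analysis. This is a cheap improvement to make before the final analysis, not a flaw that invalidates the design.

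**What to change.** Amend Randomization and blinding as follows.

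1. A study assistant replaces the arm names with neutral codes in the T0/T1/T2 efficacy file and keeps the key. One assistant evaluated the first round and one co-developed the materials; if there is an assistant who did neither, that person is preferable.
2. Session and intersession process data stay out of this file, because they exist only for PPT and CBT and would reveal the control arm. Therapist and group identifiers are left out or coded too, because authors lead the control groups.
3. The principal investigator finalises and date-stamps the efficacy script on the coded data, covering lead scale, contrast, time point, model and exclusions. Only then are the codes opened.
4. State whether first-round participants count toward the 165. If they do, report the primary contrast with and without them as a sensitivity analysis.

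Cost: a few hours of existing staff time and a deposited script, with no change to recruitment or treatment. The analysis must be fixed before arm results are seen. Masking will be imperfect, since the principal investigator knows the trial and may guess an arm from the data, but the dated script still protects the main choices.

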### Interventions

The first step in conducting the study was the development of the treatment manuals and therapy materials. Two treatment manuals were developed, one each for PPT and CBT treatment. The PPT manual is based on the official PPT manual by [10] and adapted for the study. Because of economic reasons instead of 15 sessions as in the original manual, only 10 therapy sessions are conducted in the present study. In addition, the individual PPT topics were adapted and exercises from the personal PPT application repertoire of the study leaders were incorporated. As in the original manual, a gratitude diary will be filled out daily by the participants accompanying the therapy. In the individual sessions, various positive-psychological interventions are carried out, e.g., participants learn how to handle and use positive emotions, work out their personal character strengths and learn how to use them in concrete anxiety situations. Other topics covered in the PPT treatment include gratitude, optimism, a positive self-image, self-compassion, resilience, everest goals, best-possible self, and future perspective. The CBT manual is conceptually adapted to the PPT treatment and also comprises 10 therapy sessions. The exercises and content were selected based on the German language therapy tools for anxiety disorders by [56]. In the CBT treatment, participants are required to practice the relaxation exercise Progressive Muscle Relaxation according to Jacobsen on a daily basis. In CBT treatment, participants learn how to deal with anxiety thoughts and behavior and how to restructure stressful anxiety related cognitions. For this purpose, various cognitive-behavioral therapy interventions are carried out, e.g., the development of an individual explanatory model, the worry chair and various attention and breathing exercises. An elementary part of the treatment is an exposure exercise, which is worked towards during therapy. Other topics covered in CBT treatment include the three levels of anxiety (body, thoughts, behavior), the vicious cycle of anxiety, and mindfulness. In addition to the treatment manuals, workbooks were created for the participants to work on during the therapy. The workbooks contain all organizational details, theoretical topics as well as all exercises and worksheets that must be done in the video-supported sessions or as homework. Additional websites (created by Webflow) were provided for both intervention groups to make additional therapy tools available, such as videos or questionnaires. That aside the websites are also used to conduct part of the data collection. The implementation of the treatments takes place online via videoconferencing using the Zoom platform. Participants in the two intervention conditions (PPT & CBT) will meet once a week with the treatment providers for a 120-minute online presence meeting, in which the content of the respective sessions will be conducted according to the manual. In addition, participants will be given homework assignments to complete independently for the week between the face-to-face sessions. These homework assignments will be discussed in the group at the beginning of each session. The control group is designed as a PPT with minimal therapeutic supervision. The participants will receive the same PPT workbook as the intervention group and accordingly will work on the same topics and exercises over the ten weeks as the participants in the PPT intervention group. The difference between the two groups lies in the therapeutic support. In the control group, a video-supported meeting with the therapist will be held only three times: In the first session, halfway through therapy in the fifth session, and in the last session. In between, participants receive an overview email at the beginning of the week and a reminder email at the end of the week. Apart from the possibility of mail contact with the therapists, the participants in the control group carry out the exercises independently with the help of the workbook and the materials on the website. For the control group, as for the intervention groups, a separate website is provided. Another important component of all treatment conditions is the formation of teams of two clients (couple teams) within each therapy group. These teams will be formed in the first session of therapy and will remain in place throughout the duration of therapy. Participants are encouraged to meet at least once a week to discuss the week’s exercises and topics with each other. In some cases, specific reflection questions will be provided in the individual exercises in the workbook. Depending on the possibilities of the participants, the meeting could take place online via a telephone call or video call or in person. When forming the couple teams, deliberate care was taken to divide the participants according to local proximity.

### Outcome measures

Proposed psychological outcome measures are as follows. All named questionnaires are based on self-report.

#### Primary outcome measures

extent of anxiety as measured by self-report questionnaires
Beck Anxiety Inventory German version (BAI; [57])Panic and Agoraphobia Scale German version (PAS; [58])Generalized Anxiety Disorder 7 German version (GAD-7; [59])Fear Questionnaire German version (FQ; [60])subjective experience of happiness
Positive Psychotherapy Inventory German version (PPTI; [10])Flourishing Scale German version (FS; [61])quality of life
Satisfaction with Life Scale German version (SWLS; [62])

For additional third-party assessment of the level of anxiety a questionnaire designed by the authors was used (the following topics were queried: tension, anxious mood, fear, sleep disturbance, depressiveness, anxious behavior, physical symptomatology, psychological distress, impairment in living, life satisfaction, motivation & energy).

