Key inclusion and exclusion criteria	Ages eligible for study: between 18 and 65 years, Sexes eligible for study: both, Inclusion: sufficient intellectual capacity and knowledge of the German language, presence of one of the following disorder diagnoses according to F41.0 panic disorder with and without agoraphobia and/or, F41.1 generalized anxiety disorder and/or, F40.1 social phobia, Exclusion: concurrent or planned participation in psychotherapeutic or psychological treatment or counseling or participation in other psychological group services in the following three months, presence of one or more of the following disorders: major depressive episode, bipolar affective disorder or mania (current as well as history), schizophrenic or schizoaffective disorder, grief reaction, severe anorexia or bulimia, substance dependence (alcohol, illicit drugs), severe Personality Disorder; acute suicidality; use of psychotropic drugs itself not a criterion for exclusion, but a change in medication, a change in dose, or complete discontinuation of the drug in the past or next three months
Study type	Interventional, randomized control study, masking: none, primary purpose: comparative therapy quality assessment
Date of first enrollment	Planned: March, 1^st^ 2022
Target sample size	165
Recruitment status	Recruiting
Primary outcomes	Extent of anxiety, subjective experience of happiness, quality of life
Key secondary outcome	General psychological distress

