**Fig 2 pone.0299803.g002:**
[figure not shown]
SPIRIT schedule of enrollment.

**Table 2 pone.0299803.t002:** Diagnostic materials.

Assessments	Study period						
	Prescreening	Screening	PRE evaluation (T0) Before session	Intervention (10 weeks) After session		POST evaluation (T1)	FOLLOW-UP evaluation (T2, after 3 months)
				Before session	After session		
BAI	×		×			×	×
PAS	×		×			×	×
GAD-7	×		×			×	×
FQ	×		×			×	×
PPTI			×			×	×
FS			×			×	×
SWLS			×			×	×
ISR			×			×	×
PHQ-9			×			×	×
STU-P					×		×
ISF				×			
MINI-DIPS		×					
PSS-K		×					
Informed consent		×					
Third-party evaluation by therapists		After screening	Before therapy			After therapy	

BAI: Beck Anxiety Inventar, PAS: Panic and Agoraphobia Scale, GAD-7: Generalized Anxiety Diagnostic, FQ: Fear Questionnaire, PPTI: Positive Psychotherapy Inventory, FS: Flourishing Scale, SWLS: Satisfaction with Life Scale, ISR: ICD-10 Symptom Rating, PHQ-9: Patient Health Questionnaire, STU-P Patient Session-Assessment Questionnaire (ger. orig.: “Stunden Beurteilungsbogen für Patienten”), ISF: Intersession-Questionnaire (ger. orig.: “Intersession Fragebogen”), MINI-DIPS: Diagnostic short interview for mental disorders (ger. orig.: “Diagnostisches Kurzinterview bei psychischen Störungen”), PSS-K: Personality Disorder Screening—Short Form (ger. orig.: “Persönlichkeitsstörung-Screening—Kurzform”)

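### The therapist-rated anxiety form listed with the primary outcomes is open to rater bias that differs by arm, and should not support any comparison with control

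*Protocol article*

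**What the plan says.** The section Primary outcome measures defines the anxiety outcome as "extent of anxiety as measured by self-report questionnaires" and lists four published scales, followed by scales for happiness and quality of life. A closing paragraph under the same heading then says: "For additional third-party assessment of the level of anxiety a questionnaire designed by the authors was used". It lists eleven topics and, unlike the scales above it, cites no source.

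Table 2 names the raters in the row "Third-party evaluation by therapists" and places the ratings after screening, before therapy and after therapy. There is no entry at the three-month follow-up.

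On who treats whom, Randomization and blinding says: "The authors, who also act as therapists, will conduct the control group". The same section has externally recruited therapists taking the treatment conditions. On contact, Interventions says: "In the control group, a video-supported meeting with the therapist will be held only three times". PPT and CBT patients have ten sessions, one a week, of 120 minutes each. Table 1 gives the study type as "Interventional, randomized control study, masking: none".

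The opening of Outcome measures states: "All named questionnaires are based on self-report".

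**The concern.** A measure presented as third-party, under the primary heading, will be read as independent support for the self-report results. Here the third party appears to be the person who delivered the treatment and knows the arm. That alone is a common weakness of therapist ratings. What makes it worse in this trial is that the type of rater changes with arm, and it changes exactly at the contrast in the main research question: PPT and CBT against PPT with minimal support.

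A difference on this form between control and either active arm could come from treatment, from authors rating instead of external therapists, or from judging a patient after three meetings instead of ten. If the form were reported as confirming efficacy, the trial could claim corroboration that its design cannot supply.

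**Working it through.** The plan gives no figure for this measure, so the check sets the statements side by side and then shows what kind of rater error would matter.

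**1. Raters and contact by arm**

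| | PPT | CBT | Control |
|---|---|---|---|
| Group led by (Randomization and blinding) | external therapists | external therapists | the authors |
| Meetings (Interventions) | 10 | 10 | 3 |
| Masking (Table 1) | none | none | none |

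Ratio of meetings: 10 / 3 = 3.3. External therapists are said to be assigned blindly, but that describes how they are allocated; a therapist cannot be unaware of the treatment being delivered. Trial governance adds that the therapists were trained in both manuals, so PPT and CBT draw on one pool with equal contact.

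**2. The inference needed.** Table 2 says only that therapists rate. That the treating therapist gives the after-therapy rating is the natural reading, since that therapist has observed the patient, but it is not stated. On that reading, and if the stated allocation of therapists is kept, no rater scores both control and active patients. Rater type is then completely confounded with the control contrast, and adjusting for rater cannot help.

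**3. What survives in a change score.** Write each rating as true level plus a rater error, with mean error *e* in each arm at each time. The bias in an active-minus-control difference in pre-post change is

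(e_post − e_pre) in the active arm − (e_post − e_pre) in control.

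If the same person rates before and after with a constant tendency, each bracket is zero and so is the bias. It is not zero if the rater changes between the two times, or if the rater's tendency moves over therapy because of expectation, stake or amount of contact, and does so differently by arm.

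The article does not settle which case applies. Screening is done by psychologists and master students (Participant recruitment process), but the therapists were also trained for screenings (Trial governance), and Table 2 has a before-therapy rating as well. The after-screening rating precedes randomization, so it cannot be influenced by arm.

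**4. Illustration with assumed values.** Take 55 per arm (Sample size), no true effect, a two-sided 5% pairwise test, and a residual rater shift of *b* SD of the analysed score, meaning what is left after any cancellation in step 3. With s = b / √(2/55) = b / 0.1907,

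P(reject) = 1 − Φ(1.96 − s) + Φ(−1.96 − s).

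| Assumed b | s | P(reject) |
|---|---|---|
| 0 | 0 | 5% |
| 0.1 | 0.52 | 8% |
| 0.2 | 1.05 | 18% |
| 0.3 | 1.57 | 35% |
| 0.5 | 2.62 | 75% |

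No value of *b* is in the document. The table shows only that a modest residual shift would be enough to mislead.

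**The case against.** The strongest reply is that the form is not really a primary outcome. It is called additional, the anxiety outcome is defined by self-report scales, the registered list in Table 1 is "Extent of anxiety, subjective experience of happiness, quality of life" without naming the form, and Statistical analysis does not mention it. The process questionnaires follow in the same kind of trailing paragraph under Secondary outcome measures. All of this stands, and it limits the point to a supporting measure. It does not remove the point, because the placement and the third-party label invite use as corroboration and nothing states the form's role.

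A second reply is that a rater difference need not reach the result, because change is analysed. This also stands where the same person rates both times with a constant tendency. A reader might infer that any shift between authors and external therapists would appear in full as a treatment effect; step 3 of the working shows why the document does not support that.

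Other stronger readings also fail:

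- **The trial's primary result is biased by this form.** The self-report scales do not pass through the therapist.
- **The bias favours the active arms.** Authors rating their own control patients could err in either direction.
- **Early and late ratings come from different people.** This is possible but not stated.
- **The form does not measure anxiety.** It includes life satisfaction, motivation and energy, and depressiveness, but most topics are anxiety or distress content, and scoring may be set out in a fuller document.
- **The missing follow-up rating is an error.** It fits a supporting measure.

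On the self-report sentence, it can be argued that the form has no name and so is not among the named questionnaires. That makes the inconsistency mild, but a short exception would remove it.

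**Conclusion.** The concern holds for the therapist form and only for it. Comparisons with control on this form are open to differential bias by arm that no analysis can separate from treatment. This rests on one inference, that treating therapists give the after-therapy rating, and on the authors alone leading the control groups, as planned. Neither size nor direction can be derived from the document; the rejection rates in the working are illustrations under assumed shifts. PPT versus CBT is less exposed, because raters come from the same pool with equal contact, but they still know the treatment they are scoring. The sample size, the stated analysis and the self-report primary outcomes are untouched. What changes is what the trial may claim from this measure.

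**What to change.** - Move the form out of Primary outcome measures, and label it exploratory and rated by unblinded therapists.
- State that it will not be used to support efficacy or any comparison with the control arm.
- Keep any PPT versus CBT use descriptive, with a note that the raters know the treatment.
- Amend the opening sentence of Outcome measures so that it excepts this form from the statement that the questionnaires are self-report.

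The cost is protocol wording only; no new data collection is needed. The downside is that the trial no longer presents a third-party measure beside its self-report primary outcomes.
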